## **12. Main outcome measures**

The primary outcome measures are changes in the 15-item Incremental Behavior Change towards Smoking Cessation (IBC-S) (25), which detects behavioral progression towards smoking cessation, and tobacco abstinence in the past 7 days at 3-month follow-up, which is validated using exhaled carbon monoxide (<4 ppm) and salivary cotinine (<30 ng/ml). The secondary outcome measures are (1) self-reported use of smoking cessation service or medication since baseline at 3 and 6-month follow-up; (2) self-report 7-day abstinence at 3 and 6-month follow-up; (3) biochemical validated abstinence at 6-month follow-up. Feasibility measures include the satisfaction score towards the intervention and the EMA compliance.

## **13. Follow-up**

All participants will be followed up via telephone by an allocation-blinded interviewer at 3 and 6 months after consenting to participation. Only the participants who report abstinence in the past 7 days will be invited for measurement of their exhaled CO with a Smokerlyzer and salivary

cotinine with a cotinine saliva test device at their residence, workplace, or nearby, according to their preference. To increase participation, the participants will be given HK\$50 (approximately equivalent to US\$6.4) as a compensation for their time cost. All participants will not know the validation incentive at baseline. The validation takes a very short time (15 seconds) and is easy. Participants' satisfaction toward EMA app and EMA questionnaire will be assessed via telephone one week after the compliance of the EMA period. The satisfaction toward EMA will be evaluated by the nurse-phone call for the intervention group and by our allocation-blinded interviewer for the control group.

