## **10. Blinding**

Participants will not be blinded to the intervention. Assessors of the follow-up outcomes and the research investigators will not be involved in the recruitment and intervention delivery and will be blinded to the group allocation (single-blinded design).

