Participants will be encouraged to improve compliance via WhatsApp reminders if their compliance rate drops to 50% or below in the first 3 study days. To increase uptake and compensate the time spent by the participants, a small amount of cash incentive is needed. All participants will be given a HK\$50 gift voucher for the completion of baseline survey. They will be rewarded a HK\$ 15 gift voucher for completing 3 time-based EMA surveys within each day. They will be further rewarded a HK\$ 10 gift voucher for completing all surveys in each day. In addition, participants will be further rewarded HK\$ 25 gift voucher for completing more than 80% of 7 days time-based EMA surveys. Participants who complete biochemical validation at 3 months or 6 months follow up will obtain an additional HK\$50 gift voucher.

**EMA-based intervention** Based on the EMA of each participant, a trained research nurse will review their (1) nicotine dependence; (2) intensity and frequency of reported cravings; and (3) the impact of exposure to pro-smoking cues on smoking behaviors. A personalized quit plan will be developed based on tailored suggestions from the US clinical practice guideline for smoking cessation, Smoking Cessation, Smoking Cessation Information Kit (published by Department of Health), the theory of Health Action Process Approach, and the self-determination theory. Our recent studies showed that interventions based on these theories are effective (22, 24). Half of the randomly selected participants (intervention group) will receive this quit plan via a nurse-led phone call, email, and WhatsApp. The nurse will then design a quit plan including (1) self-help techniques on handling craving; (2) suggestions to avoid the reported pro-smoking cues; (3) whether to quit progressively or abruptly; (4) referral for existing smoking cessation service; and (5) instruction of using over-the-counter (OTC) nicotine replacement therapy (NRT), if OTC-NRT is preferred by the participant. Participants will then receive tailored quitting reminders via instant messaging social media (i.e., WhatsApp, WeChat) and voluntarily discuss their quit plan with the nurse in the subsequent 10 weeks.

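### The satisfaction call is assigned by arm, so the interviewer described as allocation-blinded learns who the controls are before the 3-month assessment

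*Protocol*

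**What the plan says.** Section 10 of the protocol leaves participants unblinded and places the blinding with assessors and investigators: "Assessors of the follow-up outcomes and the research investigators will not be involved in the recruitment and intervention delivery and will be blinded" to allocation. Section 13 repeats the commitment for the outcome calls, in which all participants are to be "followed up via telephone by an allocation-blinded interviewer at 3 and 6 months after consenting to participation".

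The same section adds an earlier call on satisfaction with the EMA app and questionnaire, which "will be assessed via telephone one week after the compliance of the EMA period". It then divides that call by arm: "The satisfaction toward EMA will be evaluated by the nurse-phone call for the intervention group and by our allocation-blinded interviewer for the control group".

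The nurse is the person who delivers the intervention. Under Section 11 the intervention group "will receive this quit plan via a nurse-led phone call, email, and WhatsApp", followed by ten weeks of reminders and optional discussion with the nurse. Section 12 gives satisfaction a descriptive role: "Feasibility measures include the satisfaction score towards the intervention and the EMA compliance".

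**The concern.** Calling someone allocation-blinded while giving that person a call list from one arm only is a contradiction. The list itself discloses the allocation, and it does so before the primary outcomes are collected.

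IBC-S is a primary outcome, follow-up is by telephone, and the protocol gives no objective check on the scale. Seven-day abstinence is also asked by telephone. It is a secondary outcome in its own right, and under Section 13 only those who report abstinence are invited for CO and cotinine measurement. An interviewer who knows the arm may probe, prompt or code differently, even without intending to, and no later analysis can restore blinding lost in this way.

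A second, smaller matter is that the person asking about satisfaction differs systematically between the arms.

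**Working it through.** The protocol gives no figure to reproduce on this point. The check sets its sections side by side.

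**1. Who calls whom, and when**

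| Call | Intervention group | Control group | Timing |
|---|---|---|---|
| EMA satisfaction (Section 13) | Nurse | Allocation-blinded interviewer | One week after the 7-day EMA period |
| Outcomes (Section 13) | Allocation-blinded interviewer | Allocation-blinded interviewer | 3 and 6 months after consent |

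If the EMA week starts promptly after consent, the satisfaction call falls at about day 7 + 7 = 14. Taking 3 months as 90 days, that is 90 − 14 = 76 days, or about 2.5 months, before the primary assessment. Participants choose their own EMA week, so the gap will vary.

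**2. What the interviewer learns**

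Under the split rule every person the interviewer calls about satisfaction is a control. With 440 planned (Section 7) and 1:1 allocation (Section 9), that is up to about 440 / 2 = 220 people. The figure is approximate because simple randomisation need not split evenly and not every control will be reached. Anyone not called could be inferred to be in the intervention group, but only by an interviewer, or a pool sharing call lists, who can connect the two sets of calls.

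**3. Whether this reaches the 3-month outcomes**

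It does if the same interviewer or pool makes both calls. Section 13 uses the same label for both. Section 10 keeps outcome assessors out of recruitment and intervention delivery but says nothing about satisfaction calls. The overlap is therefore the natural reading, though it is not stated.

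**4. Which outcomes are exposed**

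- IBC-S at 3 months: exposed.
- Self-reported 7-day abstinence at 3 and 6 months: exposed. Through it, the selection of people invited for validation is exposed too.
- CO and cotinine readings once taken: not exposed.

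**5. Illustration for IBC-S**

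The protocol gives no size for any reporting bias, so the values below are assumptions and show only how sensitive the test would be. Let b be a spurious between-arm shift in SD units with no true effect, and n the number per arm. Then SE = √(2/n), and the two-sided 5% rejection rate is 1 − Φ(1.96 − b/SE) + Φ(−1.96 − b/SE). For n = 220, SE = √(2/220) = 0.095. For n = 154 (220 × 0.70, an assumed retention), SE = √(2/154) = 0.114.

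| b (SD) | n = 220 | n = 154 |
|---|---|---|
| 0 | 0.050 | 0.050 |
| 0.05 | 0.082 | 0.072 |
| 0.10 | 0.182 | 0.142 |
| 0.20 | 0.555 | 0.419 |

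These rates do not show that a bias of any given size would occur.

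**6. Satisfaction**

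Arm and assessor take the same value for every participant. A model with an intercept, arm and assessor has three columns but rank 2, so no analysis can separate the two effects.

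**The case against.** The strongest reply is that the link to the primary outcomes is inferred. The protocol does not say that the same person makes the satisfaction and outcome calls. Even if so, the interviewer would have to recognise earlier contacts some 2.5 months later. This stands as a condition on the finding. It does not remove the contradiction in the satisfaction call itself, and nothing in the protocol prevents the overlap.

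Unblinded participants may also reveal their arm at follow-up, particularly when asked about use of cessation services. That is true, but occasional disclosure is different from a procedure that discloses allocation for a whole arm.

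Several stronger readings are tempting, and the document does not support them:

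- **A planned satisfaction comparison is invalidated.** Section 12 lists satisfaction as a feasibility measure, and Section 14 specifies no between-arm test of it. Description within an arm remains possible.
- **Assessor blinding is the only safeguard.** Section 10 also blinds the investigators, Section 9 keeps allocation apart from the research data, and validated abstinence requires CO and cotinine confirmation.
- **Allocation is disclosed for all 440.** This needs shared interviewers or call lists, complete calling, and recall of earlier contacts.
- **Courtesy bias affects one arm only.** The call concerns the app and questionnaire, not the nurse's quit plan, and controls also answer to study staff. A difference in degree is plausible but not shown.
- **Sections 12 and 13 measure different things.** Section 12 speaks of satisfaction with the intervention and Section 13 of the app and questionnaire. Section 11, headed as the intervention, includes the app, so this is loose wording at most.

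**Conclusion.** The concern holds in a limited form. On the face of Section 13, the interviewer who makes the control-arm satisfaction calls is not blinded to the people called, up to about 220 of them, and this precedes the 3-month assessment. That much needs no assumption beyond the interviewer knowing the rule written in the protocol.

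The consequence for IBC-S and for the self-report that leads to validation rests on one further assumption, that the same interviewer or pool makes the outcome calls. How far results would move cannot be derived from the protocol. Any between-arm comparison of satisfaction would be confounded with the person asking, but none is planned.

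This should be fixed, because a primary outcome is exposed and the remedy is simple. It is not a must-fix: the effect is conditional, the biochemical readings are objective, and satisfaction is a feasibility measure.

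**What to change.** Delete the rule in Section 13 that splits the satisfaction call by arm. Collect EMA satisfaction in the same way in both arms, by either of two routes:

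- a short Qualtrics or in-app form after the 7-day EMA period; or
- telephone calls to both arms by existing staff who make no 3- or 6-month outcome calls.

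Add one sentence to Section 10 or 13 stating that the 3- and 6-month interviewers take no part in satisfaction calls and do not see the call lists.

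The form costs a wording change and one short questionnaire, and it removes telephone work. Its drawback is possibly lower response, especially among participants who stopped using the app, whose views matter for feasibility. The pilots in Section 4 had responses to 48% and 73.5% of EMA prompts, so some loss should be expected, and Qualtrics is safer than the app for reaching those who dropped it. The telephone route keeps the present mode of collection but needs staff time outside the outcome team.

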#### **14. Statistical analysis**

Intention-to-treat approach will be used to include all consented participants in the analysis and assume non-respondents at the 3-month follow-up as smokers. Chi-squared and t-tests will be used to compare sociodemographic and smoking characteristics of participants to assess the balance between intervention and control group.

The primary comparison is the prevalence of tobacco abstinence and the score of IBC-S between the EMA-based smoking intervention group and the control group. Logistic regression model and linear regression will be used to compare the 7-day PPA and the score of IBC-S between intervention and control group at 3 months, respectively. We will also use multiple logistic regression and multiple linear regression adjusted for imbalance socio-demographic smoking characteristics assessed at baseline to account for imbalances in baseline characteristics.

We will transfer checklist options of smoking cues to binary outcomes. For example, an EMA question asked 'In the past 3 hours, have you been exposed to (check all that apply)' followed by these checklist options: family smoking; friends smoking; partner smoking; receive tobacco products from others; receive encourage of smoking from others). We will recode response into a series of dichotomous variables. Generalized estimating equation analysis will be used to examine the causal relationship between smoking cues and smoking-related behaviors in all participants. A linear mixed model will be used for the association analysis when the outcome is not binary.

Direct operating costs will include app development, salary (of nurses and research assistants), recruitment, telephone follow-up, and publicity items. Costs for study design, analysis, report

writing, and irrelevant administration will be excluded. The cost per successfully recruiting a smoker to participate will be calculated by dividing the total cost by the number of smokers who have joined. Similarly, cost per participant who use smoking cessation aids and per quitter at 3-month follow-up will be calculated.

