## **5. Hypothesis**

We hypothesize that smokers who receive the EMA-based smoking cessation intervention will have higher scores in Incremental Behavior Change towards Smoking Cessation (IBC-S), which measures the behavioral progression towards smoking cessation, and higher biochemically validated abstinence than those who do not receive the intervention at 3-month follow-up.

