## **8. Recruitment procedures**

In the outdoor recruitment sessions, the recruitment staff will approach and distribute souvenirs (e.g., a tissue pack) or leaflets to the smokers at outdoor smoking hotspots for 3-4 hours in daytime. If a smoker is willing to accept them and talk to the recruitment staff, the staff will advise the smoker to quit using the AWARD protocol and ask further questions related to eligibility. The AWARD protocol includes (1) **A**sk the smoking history, (2) **W**arn about the high risk (i.e., half of the smokers will die of smoking-related diseases), (3) **A**dvice to quit, (4) Introduce smoking cessation services and medications (**R**efer), and (5) Repeat the above advice (**D**o-it-again) (23). Our previous studies have shown that the AWARD protocol is a feasible and appropriate tool used by non-healthcare professionals to promote smoking cessation.

The promotion sessions will be organized at outdoor smoking hotspots, which will be selected from the public places in our funded project of Health Care Promotion Scheme (Project number 01170418). These locations cover New Territories, Kowloon, and Hong Kong Island, and the feasibility study supports that the number of subjects recruited in these locations will be higher than that in other places. Thus, they will be used in this study. Pre-promotion site visits and replacement of hotspots with reduced number of smokers will be done to ensure that the maximum number of smokers can be approached.

Eligible participants will be given more details of the study, and asked to consent to participation via an online form on Qualtrics. Then, the staff will assist the participants to install the EMA app on their mobile phones. Participants will need to complete a simple baseline questionnaire, which documents sociodemographic characteristics, smoking cues, smoking behaviours and contact information. Afterwards, the staff will ask the participants to select 7 consecutive days as the study period. Participants will be asked to set up the time they would like to receive the first time-based EMA from 6:00 am to 12:00 nn to undertake the regularly prompting EMA. For example, if a participant set the first prompt time at 9:00 am, he will be asked to complete an EMA survey at 9:00 am, 12:00 nn, 3:00 pm, 6:00 pm and an EoD survey at 9:00 pm. Then the staff will set up the EMA schedule in the app for the participants.

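### The IBC-S primary outcome is defined as a change but tested as a 3-month score, and the intention-to-treat rule gives non-respondents no IBC-S value

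*Protocol*

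**What the plan says.** Protocol Section 12 (Main outcome measures) states: "The primary outcome measures are changes in the 15-item Incremental Behavior Change towards Smoking Cessation (IBC-S"). The second primary outcome is validated 7-day abstinence at 3 months.

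Section 5 (Hypothesis) says that the intervention group "will have higher scores in Incremental Behavior Change towards Smoking Cessation (IBC-S), which measures the behavioral progression towards smoking cessation". That is a higher score at 3 months, not a larger change.

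Section 14 (Statistical analysis) follows Section 5: "The primary comparison is the prevalence of tobacco abstinence and the score of IBC-S". The models for the 3-month time point are then named: "Logistic regression model and linear regression will be used to compare the 7-day PPA and the score of IBC-S between intervention and control group". A second, multiple regression adjusts for sociodemographic and smoking characteristics that turn out imbalanced at baseline. Baseline IBC-S is not named in either model.

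Section 8 (Recruitment procedures) describes the baseline data: "Participants will need to complete a simple baseline questionnaire, which documents sociodemographic characteristics, smoking cues, smoking behaviours and contact information". IBC-S is not mentioned there.

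On missing follow-up, Section 14 has one sentence: "Intention-to-treat approach will be used to include all consented participants in the analysis and assume non-respondents at the 3-month follow-up as smokers".

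**The concern.** Two parts of the text do not fit together.

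First, a change from baseline and a score at 3 months are different variables. A change needs IBC-S measured twice, and the protocol mentions only the later measurement. If IBC-S is not taken at baseline, the outcome in Section 12 cannot be recovered afterwards. If it is taken, the plan leaves open whether the primary test uses the score, the change, or the score adjusted for baseline. These three differ in precision, and the choice could be made after the data are seen.

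Second, the promise to include everyone who consented rests on a single rule. Treating a non-respondent as a smoker settles the abstinence outcome. It gives no value on a 15-item scale of progress towards quitting, because people who still smoke can differ in how far they have moved. As written, the linear regression has no value to use for non-respondents, so it cannot meet the intention-to-treat statement. This matters if loss to follow-up is related to progress or to arm. Differential loss is plausible: participants are not blinded (Section 10), and only the intervention arm has nurse contact and ten weeks of reminders (Section 11).

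**Working it through.** **No power figure to reproduce.** Section 7 sets the target at 440 participants in 11 months from recruitment capacity: 440 / 11 = 40 per month, inside the stated 30 to 60. The protocol gives no alpha, power, standard deviation, target IBC-S difference or dropout rate. Everything below that needs these is an assumption.

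**Step 1: does the choice between change and score alter the expected effect?** Let Y0 and Y1 be IBC-S at baseline and 3 months. The expected arm difference in change is

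[E(Y1, intervention) − E(Y1, control)] − [E(Y0, intervention) − E(Y0, control)].

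Allocation is randomised 1:1 and concealed at recruitment (Section 9), when baseline data are taken, so the second bracket is zero in expectation. With full follow-up, both analyses estimate the same effect.

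**Step 2: does it alter precision?** Inputs: 220 per arm (440 / 2, from Sections 6 and 7); assumed two-sided alpha 0.05, 80% power and full follow-up; assumed correlation r of 0.3 to 0.7 between baseline and 3-month scores, with equal SDs.

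Detectable difference in SD units = (1.96 + 0.8416) × √(2/220) × √f, where f is 1 for the 3-month score, 2(1 − r) for change, and 1 − r² for regression on arm with baseline as covariate (ANCOVA).

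| Analysis | r = 0.3 | r = 0.5 | r = 0.7 |
|---|---|---|---|
| 3-month score | 0.267 | 0.267 | 0.267 |
| Change | 0.316 | 0.267 | 0.207 |
| ANCOVA | 0.255 | 0.231 | 0.191 |

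The change score is less precise than the plain score at r = 0.3, equal at 0.5 and more precise at 0.7. ANCOVA is the most precise of the three throughout this range. For a true effect of 0.267 SD, power is 80% for the score; 66%, 80% and 95% for change; and 84%, 90% and 98% for ANCOVA.

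**Step 3: what does the non-response rule supply?**
- Abstinence: the non-respondent is set to not abstinent. The rule is complete.
- IBC-S: no value is assigned. The rule is silent.

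If the regression then used only observed scores, an assumed 20%, 30% or 40% non-response would leave 176, 154 or 132 per arm, that is 352, 308 or 264 of the 440. The detectable difference for the plain 3-month score would be 0.299, 0.319 or 0.345 SD, and power at 0.267 SD would be 71%, 65% or 58%. Non-response loses information whatever rule is used. These figures show how far the analysed group could be from the 440 that the text implies; they are not a loss that a better rule would fully recover.

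**The case against.** The strongest reply is that Section 12 may only be loosely worded. Both Sections 5 and 12 describe IBC-S as measuring progression towards cessation, so a single 3-month score may already express change. The documents do not give the scoring. That reply may well be right. It makes the repair smaller, but the sections still disagree today.

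A reader might go further than the documents allow in several ways:
- **Bias, or two different effects.** A reader might infer that omitting baseline IBC-S biases the comparison, or that change and score target different effects. Step 1 shows otherwise under randomisation with full follow-up. What differs is precision, and whether the defined variable can be computed.
- **Baseline IBC-S is certainly not collected.** Section 8 gives broad headings, not an item list, and smoking behaviours could cover it. The text supports only that it is not named.
- **The analysis is purely unadjusted.** A covariate-adjusted regression is also planned. The fair criticism is that it selects covariates by observed imbalance and does not name baseline IBC-S.
- **A complete-case analysis is planned.** The protocol does not say so, and imputation detail may properly sit in an SAP. The fault is narrower: the protocol makes a promise about its analysis set and gives one rule, which cannot deliver that promise for this outcome.
- **A change score always costs power.** It does so only for r below 0.5 under the equal-SD assumption.

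It is also fair to say that adding 15 items at baseline conflicts with Section 8, which calls the questionnaire simple and requires recruitment at hotspots to be brief. A baseline IBC-S is desirable but is not needed for the point to stand.

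**Conclusion.** The point holds as an inconsistency in the stated text. One of the two primary outcomes is a change in Section 12 and a 3-month score in Sections 5 and 14, with no baseline IBC-S named anywhere. It may therefore not be computable as defined. The intention-to-treat sentence cannot be met for IBC-S as written.

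The consequence of the first part is an ambiguous primary variable and uncertain precision, not bias. Detectable differences run from 0.191 to 0.316 SD across the three possible analyses, against 0.267 SD for the 3-month score that Section 14 names. That range depends wholly on the assumed alpha, power, full follow-up and r of 0.3 to 0.7. The consequence of the second part cannot be sized from the documents because they give no expected non-response. Any bias would depend on how loss relates to progress and arm. Both parts should be corrected, and most of the correction is wording.

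**What to change.** 1. Use one definition in Sections 5, 12 and 14: IBC-S score at 3 months.
2. State whether IBC-S is measured at baseline. If it is or can be, make the primary analysis a linear regression of the 3-month score on arm with baseline IBC-S as a prespecified covariate. If not, delete the reference to changes in Section 12 and keep the 3-month comparison.
3. Restrict the rule that non-respondents are smokers to the abstinence outcomes.
4. For missing IBC-S, either use multiple imputation by arm from the baseline and EMA-week data already collected, with a sensitivity analysis that gives non-respondents a score representing no progress, or state openly that the IBC-S analysis set is respondents only and drop the claim that everyone who consented is included.

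Cost: items 1 and 3 are wording. Item 4 adds modest analysis work. The no-progress analysis is conservative only if loss is not heavier in the control arm, so loss should be reported by arm beside it. Item 2 costs nothing if IBC-S is already collected or the reference to changes is deleted. Adding it means up to 15 extra items in a recruitment procedure meant to be brief, which the sponsor should weigh against the gain in precision.

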## **7. Subjects**

This proposed study aims to recruit daily tobacco users, regardless of intention to quit. We shall send mass emails to the University of Hong Kong (HKU) staff and students, post recruitment advertisements in media and smoking cessation clinics, or actively invite smokers at outdoor smoking hotspots to participate. Outdoor smoking hotspots (i.e., urban places with a butt

collector and a cluster of smokers) were shown as feasible platforms for efficient smokers' recruitment (21). The inclusion criteria are: (1) daily consumption of tobacco products (including traditional cigarettes, electronic cigarettes, and heated tobacco products) in the past week; (2) age  $\geq 18$  years; (3) owning a mobile smartphone with internet access; (4) staying in Hong Kong during the 1-week EMA study period; and (5) able to read and write Chinese. To confirm the smoking status of the participants, exhaled carbon monoxide will be measured and required to be 4ppm or above, or saliva cotinine to be 30ng/ml or above. Because the proposed study aims to promote smoking cessation in smokers who do not plan to use smoking cessation aids, we will exclude smokers who (1) plan to use smoking cessation services or medication in the coming month or (2) using smoking cessation services, or using nicotine replacement therapy in the past 7 days. Smokers who reported having mental illnesses and female smokers who are pregnant are also excluded as they need more specific smoking cessation intervention.

To date, there have been no randomized controlled trial (RCT) to provide an estimate of effect size for the EMA-based intervention. Our team's previous RCT of testing a personalized smoking cessation intervention showed that the effect size (risk ratio) can be as high as 1.68 (22). Our current outreach health promotion (funded by Health Care Promotion Scheme, project no. 01170418) showed that each month we can recruit 30 to 60 smokers to participate in the smoking cessation RCT. Considering the limited study period covered in this funding application, this proposed study targets to recruit 440 smokers in 11 months.

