## **9. Randomization and allocation concealment**

Simple individual randomization (1:1 allocation ratio) will be applied. Qualtrics' randomizer will be used for random allocation. This will be implemented by a research staff, who is not involved in the recruitment, so that all recruitment staff and participants will be concealed to the group allocation at recruitment. After a participant consent to the trial, our research staff will access the randomizer in Qualtrics and enter the individual participant's 5-digit identifier. With the randomizer feature in place, Qualtrics will display a page indicating either the intervention group or the control group. A separate Qualtrics account for the randomizer will be used, and group allocation will be separated from research data. Information of the participants in the intervention group will be transferred to the research nurse for the EMA-based intervention.

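### The additional adjusted models take their covariates from chance baseline imbalance, so strong predictors will usually be left out, and the plan does not say which model decides

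*Protocol*

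**What the plan says.** All of this is in Protocol Section 14 unless noted.

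- Baseline comparison: "Chi-squared and t-tests will be used to compare sociodemographic and smoking characteristics of participants to assess the balance between intervention and control group".
- First-listed models for the 3-month primary outcomes: "Logistic regression model and linear regression will be used to compare the 7-day PPA and the score of IBC-S between intervention and control group". No covariates are named.
- Adjusted models, given in addition: "multiple logistic regression and multiple linear regression adjusted for imbalance socio-demographic smoking characteristics assessed at baseline to account for imbalances". No variable is named, and neither a prognostic criterion nor a threshold for imbalance is given.
- Allocation (Section 9): "Simple individual randomization (1:1 allocation ratio) will be applied". There is no stratification.
- Size (Section 7): "this proposed study targets to recruit 440 smokers in 11 months". The supporting text gives a risk ratio from an earlier trial and a monthly recruitment rate, but no power calculation.

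**The concern.** The Protocol states a rule for choosing covariates: adjust for what turns out imbalanced. With concealed simple randomization, a test of baseline balance tests a null hypothesis known to be true. A flagged variable is one that happened to differ between arms, which has no bearing on whether it predicts quitting or IBC-S. A strong predictor gets in only by luck, and the content of the adjusted model is unknown until the data are in hand.

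What is at stake is precision. Allocation is unstratified and the target of 440 rests on recruitment capacity, so adjustment for variables fixed in advance is an inexpensive way to gain precision. The plan gives most of that up. It also leaves two estimates for each primary outcome without saying which one carries the conclusion if they differ.

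**Working it through.** The plan gives no figure to reproduce here. The target of 440 over 11 months is 440/11 = 40 per month, inside the range implied by "each month we can recruit 30 to 60 smokers to participate in the smoking cessation RCT". It is a capacity figure.

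**Inputs from the Protocol:** 440 participants, 1:1, simple randomization, imbalance judged by chi-squared and t-tests.

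**Assumptions not in the Protocol:** a 5% threshold for imbalance; 10 to 20 independent baseline variables tested; the share of outcome variance explained by the prognostic covariate; a continuous outcome with a treatment effect of 0.267 SD, which gives about 80% power unadjusted with 440.

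**1. Chance of at least one flagged variable**, 1 − 0.95^k:
- k = 10: 1 − 0.95^10 = 40%
- k = 15: 1 − 0.95^15 = 54%, with 15 × 0.05 = 0.75 flagged on average
- k = 20: 1 − 0.95^20 = 64%

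**2. Chance that a given strong predictor is flagged.** This is 5% by construction, so it is left out 95% of the time. A simulation (440 participants, 10 covariates of which one is prognostic, 4,000 runs per setting) flagged it in 4.4 to 5.3% of runs.

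**3. Power in the same simulation:**

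| Variance explained | Unadjusted | Covariates chosen by baseline p < 0.05 | Prognostic covariate fixed in advance |
|---|---|---|---|
| 10% | 79% | 79% | 84% |
| 20% | 79% | 79% | 87% |
| 30% | 80% | 81% | 91% |
| 40% | 81% | 83% | 95% |

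Selection by baseline test gains almost nothing over no adjustment. A fixed covariate gains about 4 to 13 percentage points over selection.

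**4. Type I error.** Under the null the rejection rate was 4.4 to 4.8% unadjusted, 3.7 to 4.4% with test-based selection and 5.0 to 5.5% with the fixed covariate. In a second simulation (10 or 15 covariates, 5,000 runs per setting), claiming success if either the crude or the adjusted model was significant gave 4.8 to 5.8% false positives.

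**5. Participant equivalent for IBC-S.** In a linear model, covariates explaining a share R² of variance reduce the variance of the treatment effect by the factor 1 − R², which is equivalent to N/(1 − R²) participants:
- R² = 0.20: 440/0.80 − 440 = 110
- R² = 0.25: 440/0.75 − 440 = 147

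This uses all 440 as analysed and does not carry over to the abstinence model.

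**6. Events for abstinence.** At an assumed 5 to 10% validated abstinence overall, 440 participants give 22 to 44 events, which limits how many covariates that model can carry.

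**The case against.** The strongest reply is about scope. The adjusted models are introduced as an addition, after a primary comparison whose models name no covariates. That first comparison does not depend on which variables happen to differ. This stands: the flaw is confined to the adjusted analyses.

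Second, the Protocol never says in one sentence that p-values select the covariates, and it gives no cut-off. This is also true, and the 95% and 54% figures depend on an assumed 5% threshold. But adjustment is limited to imbalanced characteristics and no other way of judging imbalance is offered, so this is the natural reading. Selecting on the observed size of the differences would still be selecting on chance.

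Third, a covariate list is commonly left to an analysis plan. Here, however, the Protocol fixes the selection rule itself, and a later plan that followed it would inherit the problem.

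A reader might infer that the two-model approach inflates false positives. The simulations do not support that: selection by baseline test is mildly conservative, and even picking the more favourable of the two models barely moves the error rate. A reader might also infer that both primary outcomes lose precision in the same way. They do not. In logistic regression, adjustment changes the odds ratio being estimated and does not shrink its standard error as in a linear model, so the participant equivalent holds for IBC-S only.

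**Conclusion.** The concern holds for the additional adjusted analyses of both primary outcomes. Their covariates are determined by chance imbalance, and a strong predictor would be missing about 95% of the time at an assumed 5% threshold. The first-listed models remain valid and there is no material inflation of type I error.

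The cost is efficiency, mainly for IBC-S: about 110 to 147 participant equivalents if covariates explain 20 to 25% of its variance. That share is an assumption; the Protocol offers no figure for it. Omission of strong predictors is likely, not certain. Separately, the Protocol does not say which model is decisive. This is worth correcting, but it does not put the primary comparison in doubt.

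**What to change.** 1. Describe baseline characteristics by arm and drop the chi-squared and t-tests.
2. Replace adjustment for imbalanced characteristics with a short list fixed now, chosen for expected prognostic value regardless of observed balance. Draw it from what is already collected before randomization. Section 8 lists sociodemographic characteristics, smoking cues and smoking behaviours in the baseline questionnaire. Daily consumption and other baseline smoking behaviours are candidates, plus recruitment channel if it is recorded.
3. Include baseline IBC-S in the IBC-S model only if it is collected at baseline. Section 12 speaks of changes in the scale, but Section 8 does not name it among the baseline items. Adding it would mean 15 items in a deliberately brief recruitment procedure. Intention to quit and past quit attempts are not named in Section 8 either. Time to first cigarette is named only in the end-of-day survey (Section 11), which follows consent, so it should not be assumed to be available at baseline.
4. Use only one or two covariates in the abstinence model, because events may be few.
5. Name one model per outcome as decisive and the other as supportive.

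The cost is wording only if the list stays within the existing questionnaire. There are two downsides: the covariates must be fixed before unblinding, and the adjusted odds ratio for abstinence is conditional, not marginal, so it should be labelled as such and not expected to match the crude one.
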